### Data collection and analysis

#### Data collection

Data will mainly be collected prospectively in three rounds of surveys and from medical records. The baseline survey will be administered by a health worker at a local hospital in the first antenatal visit after obtaining written informed consent from women who have agreed to participate in the study. The follow-up surveys will be conducted at the hospital after within 2 days of delivery by a healthcare worker. The final survey will be a phone interview at day 42 after delivery. In addition, clinical data will be collected from the local hospital.

Participant data will be collected from a paper case report form (CRF) and then entered into an electronic case report form (eCRF) (http://bjdx.clinicalcloud.com.cn/Login.aspx) for further data sorting. Data on pregnancy and neonatal outcomes will be collected from the hospital maternity records or the general medical practitioners.

#### Data management

The paper CRFs are stored at the project office in Peking University First Hospital. The personal information of the participants will be accessible only to the data management staff; other study implementation team members, including data analysts, will not have access to it.

To ensure high-quality trial conduct, data management will be carried out according to the principles of the International Conference on Harmonization Good Clinical Practice Guideline. Quality control will be carried out routinely. Data types, entries and permitted ranges for answers to every question on the eCRFs are restricted on the web-based system being used. Automatic validation checks and automatic queries are raised by the system immediately to individual sites in the case of any query. Authorized individuals from the APPEC study group may also check the data for quality and may pose manual queries to the research site. The data will be stored by the APPEC study group for 20 years after the final publication of the trial. Further details on data storage, curation and destruction are available in a separate document on request to the APPEC trial unit.

### Statistical analysis

Baseline characteristics will be calculated using Student’s *t* test, the chi-square test or Fisher’s exact test as appropriate for comparisons across groups. Data will be analysed on an intention-to-treat basis to compare primary and secondary outcomes in both groups. The primary analysis will be done with generalized estimating equation regression models of the occurrence of PE, with adjustment for the effect of the risk factors for PE at screening and the study sites. The OR with 95% CI will be calculated to quantify the treatment effect. Moreover, exploratory subgroup analysis will be performed to identify whether the effects of intervention vary with the risk factors for PE, including chronic hypertension, pre-existing diabetes, history of PE, obesity, advanced age, nulliparity and family history of PE. The initial intervention weeks of gestation (e.g., < 16 weeks vs. ≥16 weeks of gestation) and its interaction with aspirin preventive treatment will also be investigated. A *P* value < 0.05 will be considered statistically significant. Statistical analysis will be performed by a statistician using IBM SPSS Statistics version 22.0 (IBM, Armonk, NY, USA) and Stata version 11.0 (StataCorp, College Station, TX, USA) software.

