### Objective

The aim of this study is to evaluate the effect of LDA administered from early pregnancy in Chinese pregnant women with high-risk factors. The following hypothesis will be tested: The administration of LDA to pregnant women from early pregnancy (12 to 20 weeks of gestation) will reduce the occurrence of PE by 20%. Moreover, clinical information and maternal biological samples will also be collected for further mechanistic research.

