### Randomization

Randomization will be performed using a web-based computerized central randomization system, the Interactive Web Response System (http://bjdx.clinicalcloud.com.cn/Login.aspx), in a 1:1 allocation ratio. The website randomly assigns a randomization code to each participant. Eligible women will be randomized to one of the two groups. Knowledge of the treatment allocation is open to the investigators and the participants.

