### Sample size calculation

For the primary outcome indicator, “pre-eclampsia,” we assume that the estimated detection rate for PE is 20% in the control group, according to previous studies [25–27]. The occurrence of PE in the intervention group is supposed to be 16%, and thus the estimate of risk reduction with the intervention is 20%. For 80% power and a level of significance set at 0.05, 446 participants are required in each group. Thus, the total number of women required in the study is 892. Accounting for 10% withdrawal/loss to follow-up, 981 women will need to be recruited. Finally, we set the number of women to be recruited into the study at 1000 (500 per group). The power calculation was performed using PASS 2011 software (NCSS, Kaysville, UT, USA).

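### The hypothesis is a 20% reduction in the risk of pre-eclampsia, but the only effect measure named is an adjusted odds ratio, which does not directly estimate that quantity

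*Protocol article*

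**What the plan says.** Three sections of the protocol article bear on this point.

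- **Objective.** The hypothesis is that low-dose aspirin "will reduce the occurrence of PE by 20" per cent.
- **Sample size calculation.** For the control arm, "we assume that the estimated detection rate for PE is 20% in the control group". For the aspirin arm, "The occurrence of PE in the intervention group is supposed to be 16%, and thus the estimate of risk reduction with the intervention is 20" per cent. This settles that the 20% in the Objective is a relative reduction in risk, not 20 percentage points.
- **Statistical analysis.** The primary analysis is a generalized estimating equation regression for occurrence of pre-eclampsia, adjusted for baseline risk factors and hospital. Of the effect measure it says: "The OR with 95% CI will be calculated to quantify the treatment effect". The link function is not stated, but an odds ratio implies a logit link.

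The article names no risk ratio, relative risk reduction or risk difference as a planned estimate. The only decision rule is significance at the 5% level.

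**The concern.** The question is asked on one scale and answered on another. For a rare outcome this would hardly matter, because odds and risks nearly coincide. Here the women are selected for high risk and the assumed control rate is 20%, so the two scales differ visibly.

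The odds ratio is also non-collapsible. Conditioning on prognostic covariates moves it further from 1 for the same pair of overall risks, even under perfect randomisation. The planned covariates include the characteristics that define high risk at entry, so they can be expected to be prognostic.

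What is at stake is how the headline number is read. The Discussion hopes to influence guidelines, and the Background cites a 19% reduction in the rate of pre-eclampsia from an earlier meta-analysis. Readers will set the trial's estimate beside that 19% and beside the trial's own 20%. An adjusted odds ratio does not line up directly with either.

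**Working it through.** **Inputs.** Control risk p0 = 0.20 and aspirin risk p1 = 0.16 (Sample size calculation). Effect measure: adjusted odds ratio (Statistical analysis).

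**1. The plan's own effect size.**
RR = p1/p0 = 0.16/0.20 = 0.80, a relative reduction of 20%, as stated. The risk difference is 0.16 − 0.20 = −0.04, or 4 percentage points.

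**2. The same effect as an unadjusted odds ratio.**
Control odds = 0.20/0.80 = 0.250. Aspirin odds = 0.16/0.84 = 0.1905.
OR = 0.1905/0.250 = 0.762, a 23.8% reduction in odds. This is 3.8 points more than the 20% reduction in risk.

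**3. The reverse conversion.**
If the unadjusted OR is 0.80, the aspirin odds are 0.80 × 0.250 = 0.200. The risk is 0.200/1.200 = 0.1667, and RR = 0.1667/0.20 = 0.833. That is a 16.7% reduction in risk.

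**4. Dependence on the control risk.** The 20% is a planning assumption, so the conversion is repeated over a range. With RR = 0.80, OR = 0.80(1 − p0)/(1 − 0.80·p0). With OR = 0.80, RR = 0.80/(1 − 0.20·p0).

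| Control risk | OR when RR = 0.80 | RR when OR = 0.80 |
|---|---|---|
| 10% (assumed) | 0.783 | 0.816 |
| 20% (plan) | 0.762 | 0.833 |
| 30% (assumed) | 0.737 | 0.851 |

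**5. Effect of covariate adjustment.** The article gives no covariate effects, so their strength must be assumed. Let the covariates contribute a normally distributed term with standard deviation s on the log-odds scale. Choose the intercept so that the average control risk is 0.20, and the treatment coefficient so that the average aspirin risk is 0.16. The exponentiated coefficient is the conditional odds ratio.

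| s (assumed) | Conditional OR for 20% vs 16% |
|---|---|
| 0 | 0.762 |
| 0.5 | 0.754 |
| 1.0 | 0.732 |
| 1.5 | 0.700 |

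The direction is certain for prognostic covariates. The size is not: with weak covariates the shift is under 0.01, and with strong ones about 0.06.

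**6. The test.** No effect means RR = 1, OR = 1 and a risk difference of 0 all at once, so the hypothesis test is essentially the same on any of these scales.

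None of this uses the stated 446 women per group. That figure does not reproduce for 20% versus 16% (a two-sided pooled test at 80% power gives 1447 per group). It is a separate and more serious matter.

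**The case against.** The strongest reply is that nothing here is wrong. An odds ratio from an adjusted regression of a binary outcome is standard and valid, and planning on risks while estimating an odds ratio is common. The gap is also small against the precision available. At 500 per arm with 20% and 16%, the standard error of the log odds ratio is √(1/100 + 1/400 + 1/80 + 1/420) ≈ 0.166. The 95% interval around 0.76 then runs from about 0.55 to 1.05. All of that stands, and it keeps the point modest.

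It also disposes of several stronger readings.

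- **That the odds ratio overstates the benefit.** It correctly states a change in odds. It misleads only if read as a change in risk.
- **That an odds ratio of 0.80 would count as success.** The article sets no threshold on the point estimate.
- **That the result could not be compared with the 20% or the cited 19%.** A crude risk ratio follows from the event counts in each arm. It is the adjusted one that readers could not recover from those counts.
- **That the plan excludes a risk ratio or risk difference.** The article does not say that nothing else will be reported, and an analysis plan not shown here may add them.

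What remains does not depend on silence. The article names the measure that is to quantify the effect, and that measure is not the quantity in its hypothesis.

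**Conclusion.** The point holds as a mismatch between the hypothesis and the named effect measure, not as an error in the odds ratio. On the plan's own rates, the hypothesised 20% risk reduction would appear as an unadjusted odds ratio of 0.76, and an odds ratio of 0.80 would be a risk reduction of about 17%. These figures rest on the 20% control risk; the gap narrows if the true risk is lower and widens if it is higher. Adjustment adds to the gap by an amount that the article does not determine: about 0.01 to 0.06 on the odds ratio over the assumed range of covariate strength. The conclusion of the significance test is essentially unaffected. The change is worth making because it is nearly free and lets the trial answer its question on the scale on which it was asked.

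**What to change.** Keep the adjusted odds ratio and add to the Statistical analysis section, or to the analysis plan, wording such as: *The covariate-adjusted risk ratio and risk difference for pre-eclampsia, aspirin versus control, will be reported with 95% confidence intervals alongside the odds ratio, and will be used when the result is judged against the hypothesised 20% relative reduction in risk.*

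Name one method in advance. One option is standardisation from the planned adjusted logistic model: predict each woman's risk under both allocations, average, then take the ratio and the difference. The other is a log-link Poisson GEE with robust standard errors for the risk ratio, with the risk difference obtained by standardising its fitted risks.

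The cost is a sentence or two of text and slight extra analysis work, with no new data and no change to conduct. The relative effect will look slightly smaller than the odds ratio suggests.

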### Monitoring

#### Safety monitoring

Both adverse events (AEs) and serious adverse events (SAEs) will be prospectively recorded for all participants. Both will be recorded in terms of potential causality and severity. AEs will be recorded on the CRF. SAEs will be formally reported to the sponsor and principal investigator so that reasonable action can be taken. The potential causality of the AEs in relation to the experimental drug will be assessed and classified into six degrees (unrelated, unlikely to be related, possibly related, most likely related, definitely related and unable to assess), according to the guidelines of the Uppsala Monitoring Centre [29].

#### Potential complications/side effects

Data on AEs will be collected. All SAEs will be immediately reported to the project leader, who will be responsible for notifying the ethics committee, all participating investigators and the manufacturer of the study products.

## Discussion

The purpose of this APPEC study is to evaluate the effect of LDA on PE prevention in pregnant women with high-risk factors in China. As is known, PE is a serious life-threatening complication for both mother and foetus, especially in developing countries. However, there is no effective treatment for patients with PE, other than prompt delivery of the baby when severe PE develops. Therefore, an effective drug or treatment for PE would have a major beneficial impact for both maternal and perinatal health.

To our knowledge, this study is the first and largest RCT to determine the role of LDA in reducing the occurrence of PE in a Chinese population. We enrolled eligible women from 13 hospitals in 11 provinces in China, which may generally represent the whole population in China. From our study, we can learn whether routine administration of LDA is suitable for Chinese pregnant women with mixed high-risk factors. This study may influence future guidelines for the recommendation of LDA for Chinese pregnant women. Another strength of this study is that we will collect both clinical information and biological samples (serial serum samples and tissues). We will measure the circulating levels of biomarkers (such as sFlt1, sEng and PlGF) in the serial serum samples. These anti-angiogenic factors are considered to play important roles in inciting maternal endothelial dysfunction and the end-organ injury seen in PE. We will also focus on the novel mechanistic study of PE and aspirin’s preventive effect using these serial samples.

In conclusion, our study is novel in its assessment of the effect of LDA for PE prevention in a large Chinese population, which will be helpful in guiding healthcare providers regarding whether they should recommend LDA as a preventive drug to patients in China. Because there is no clear evidence that such agent is any more or less effective in reducing the relative risk for any particular subgroup, further research is needed to focus on the evaluation of LDA’s preventive effect in women with a single risk factor, such as nulliparity, chronic kidney disease, obesity and so forth. Besides, a recent study showed that aspirin’s effects on cardiovascular and oncological diseases varies with different body sizes and that a one-dose-fits-all approach to aspirin is unlikely to be optimal [30]. It is unknown whether the preventive effect of aspirin on pregnant women varies with their different body sizes. Therefore, this information should also be discussed with women at risk of PE to help them to choose a suitable dose of aspirin for PE prevention. Overall, this study will provide information for preventive treatment with aspirin in Chinese pregnant women, especially for populations with a high risk of PE.

### Trial status

The recruitment process was started from December 2016, and it is now recruiting participants. It is anticipated that the study will last for almost 3 years.

## Abbreviations

AE: Adverse event
APPEC: Low-dose Aspirin in the Prevention of Pre-Eclampsia in China
CRF: Case report form
LDA: Low-dose aspirin
PE: Pre-eclampsia
PlGF: Placental growth factor
SAE: Serious adverse event
sEng: Soluble endoglin
sFlt1: Soluble fms-like tyrosine kinase 1
SGA: Small for gestational age
SPIRIT: Standard Protocol Items: Recommendations for Interventional Trials
